## Abstract

**Background:**

Parkinson’s disease (PD) is a common neurodegenerative disorder that affects motor and non-motor functions, significantly reducing patients’ quality of life. No effective drug-based treatments are known to solve this problem. Non-drug therapies such as Yijinjing exercise have shown potential in improving cognitive and motor functions in PD patients. However, solid evidence must still be provided to support their clinical efficacy. This study aims to evaluate the clinical efficacy of Yijinjing exercise interventions in PD patients and explore the underlying mechanisms between the cognitive and motor functions in PD.

**Methods:**

This is a single-center randomized controlled trial in which 96 eligible PD patients will be randomly assigned to receive either Yijinjing exercise group or brisk walking group or control group in a ratio of 1:1:1. Interventions (Yijinjing exercise or brisk walking training, 40 min per session) will be provided in 3 sessions per week (Monday, Wednesday, Friday) for 12 weeks, with a total of 36 sessions. After the treatment, there will be a 1-month follow-up period. The primary outcomes will be measured using the Montreal Cognitive Assessment (MoCA) and the Unified Parkinson’s Disease Rating Scale motor section (UPDRS-III). Secondary outcomes include balance function, executive function, walking function, sleep quality, and quality of life. Additionally, the prefrontal cerebral and sensorimotor cortex blood oxygen signal level will be collected to explore the underlying mechanisms. All outcomes will be assessed at baseline, at the end of 12 weeks of treatment and after an additional 1-month follow-up period.

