## Methods

### Study design

This single-center randomized controlled trial will be conducted at the Second Rehabilitation Hospital of Shanghai. Prospective participants will be screened for eligibility and voluntarily signing the informed consent form after invited to participate in the trial. Participants will be randomly assigned to the Yijinjing exercise group, brisk walking group, or control group in a 1:1:1 ratio. All patients will receive routine drug treatment and monthly health education for 12 weeks, while the intervention groups will receive Yijinjing exercise or brisk walking training. The primary outcome measures will be cognitive function and motor function assessed using the Montreal Cognitive Assessment (MoCA) and the Unified Parkinson’s Disease Rating Scale motor section (UPDRS-III), respectively. Secondary outcomes will include balance function assessed using the Berg Balance Scale (BBS), executive function assessed using the Trail Making Test (TMT), walking ability assessed using the 6-min walk test (6MWT), sleep quality assessed using the Pittsburgh Sleep Quality Index (PSQI), and quality of life assessed using the Parkinson’s Disease Questionnaire 39 (PDQ-39). Exploratory outcomes will include changes in cerebral blood oxygen signals in the prefrontal cerebral and sensorimotor cortex. Outcome measures will be collected before and after the interventions and after 1 month of follow-up. The assessor and data analyst will be blinded throughout the trial. The procedure is illustrated in Figure 1 and Table 1.

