### Sample size calculation

The design of this study is novel. According to the trial design and previous literature assessment, the sample size will be calculated based on hypothetical changes in MoCA score (28) or UPDRS motor score (10) at week 12. With a power of 90% and an alpha of 5% (two-sided). The SD from our feasibility study is used and our power calculation considered our planned analysis method, by means of an analysis of covariance (ANCOVA) in which baseline measurements served as a covariates, reducing the needed sample size (29). we calculated the minimum sample size (effect size = 0.3) in MoCA score (SD = 2.07, Difference = 1.8) to be 28 participants per group and UPDRS motor score (SD = 2.55, Difference = 1.9) to be 38 through PASS software (version 15.0.5). Therefore, With a 15% dropout rate considered, a total sample size of 135 participants will be necessary.

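### The abstract randomises 96 patients but the sample-size section requires 135; at 96 the UPDRS-III primary outcome falls short of the stated 90% power

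*Protocol article*

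**What the plan says.** The Methods paragraph of the abstract states: "This is a single-center randomized controlled trial in which 96 eligible PD patients will be randomly assigned". Allocation is equal across three arms; the Study design section repeats that "Participants will be randomly assigned to the Yijinjing exercise group, brisk walking group, or control group in a 1:1:1 ratio". So 96 means 32 per group.

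The Sample size calculation section works to other figures. Its error rates are "With a power of 90% and an alpha of 5% (two-sided". For the first primary outcome it finds the minimum "in MoCA score (SD = 2.07, Difference = 1.8) to be 28 participants per group". For the second it finds the minimum for "UPDRS motor score (SD = 2.55, Difference = 1.9) to be 38 through PASS software". It then concludes: "With a 15% dropout rate considered, a total sample size of 135 participants will be necessary".

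MoCA and UPDRS-III are both named as primary outcomes in the abstract, in Study design and under Primary outcome. The Statistical analysis section makes both part of the primary comparison at 12 weeks.

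**The concern.** Both numbers are current statements of how many patients the trial will randomise, and they cannot both be right. The article describes no staged recruitment, no sample-size re-estimation and no distinction between randomised and evaluable patients that would link them. Nor is 96 the evaluable part of 135, since 135 × 0.85 = 114.75.

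Two things are at stake. If recruitment stops at 96, one of the two primary outcomes is tested with clearly less power than the plan claims, and a null UPDRS-III result would be harder to interpret. And with two published targets, a trial that ends near 96 could be read either as complete or as stopped short of 135.

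**Working it through.** **Inputs**, all from the article: two-sided alpha 5%, power 90%; MoCA difference 1.8, SD 2.07; UPDRS-III difference 1.9, SD 2.55; dropout 15%; three equal groups; totals of 96 (abstract) and 135 (Sample size calculation).

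**Step 1: reproduce the plan's per-group sizes.** For two means under the normal approximation, n per group = 2 × (1.960 + 1.282)² × (SD/difference)², and (1.960 + 1.282)² ≈ 10.51.

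- MoCA: 2 × 10.51 × (2.07/1.8)² = 27.8, so 28. This matches the plan.
- UPDRS-III: 2 × 10.51 × (2.55/1.9)² = 37.9, so 38. This matches the plan.

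The t-based versions are 29 and 39, so the plan evidently used the normal approximation or something equivalent.

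**Step 2: reproduce the plan's total.** 38/0.85 = 44.7, so 45 per group; 45 × 3 = 135. This matches. The sample-size section is therefore arithmetically sound.

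**Step 3: see what 96 provides.** 96/3 = 32 per group randomised. 96 × 0.85/3 = 27.2 per group after the planned loss. Both are below 38, and 27.2 is also just below the 28 stated for MoCA. By comparison, 135 × 0.85/3 = 38.25.

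**Step 4: power.** Under the normal approximation, power = Φ(difference/SD × √(n/2) − 1.960). The standardised differences are 1.9/2.55 = 0.745 and 1.8/2.07 = 0.870. For example, UPDRS-III at 27.2 per group: 0.745 × √13.6 − 1.960 = 0.788, and Φ(0.788) = 0.785. The t column uses the noncentral t distribution with whole patients per group.

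| Evaluable per group | UPDRS-III, normal | UPDRS-III, t | MoCA, normal | MoCA, t |
|---|---|---|---|---|
| 96 less 15% (27.2; t at 27) | 78.5% | 76.6% | 89.4% | 88.0% |
| 96, no loss (32) | 84.6% | 83.5% | 93.6% | 92.8% |
| 135 less 15% (38) | 90.1% | 89.4% | 96.6% | 96.3% |

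**Step 5: where 96 may come from.** The article does not say. One route is MoCA-only sizing with dropout added as a multiplier: 28 × 1.15 = 32.2, rounded down to 32, and 32 × 3 = 96. Dividing instead, as the article does to reach 135, gives 28/0.85 = 32.9, so 33 per group and 99 in total. This is an inference, and the finding does not depend on it.

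**The case against.** **The abstract may simply be out of date.** If the trial is recruiting to 135, no power is lost. That is plausible, because 135 is the only total the article justifies. But the article does not say so, and the abstract is where many readers take the planned enrolment. The contradiction stands; the loss of power is conditional on 96 being the working target.

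**ANCOVA could rescue 96.** The sample-size section says baseline adjustment was taken into account and lowers the number needed. It gives no baseline correlation and does not say whether its SDs are raw or already adjusted. If they are raw, an assumed correlation of 0.3, 0.5 or 0.6 lifts UPDRS-III power at 27 per group to 80%, 87% or 92% (noncentral t). So 96 would reach 90% after dropout only at a correlation of roughly 0.55 to 0.6 or more. No such value is stated, and relying on it would contradict the section's own 38 per group, which reproduces with no further reduction. What stands is that the 77% to 78% figure holds for the stated SDs used as they are.

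**The stated effect size might support 96.** The section also says "we calculated the minimum sample size (effect size = 0.3", without naming the type. Read as Cohen's f for a three-group F test, 0.3 needs 48 per group, more than either target provides.

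**The MoCA shortfall is trivial.** Agreed. On the plan's own method it is about half a percentage point (89.4% against 90%). The material deficit is in UPDRS-III.

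**Joint power is not claimed by the plan.** Also agreed. If both outcomes had to succeed, 27 per group would give 0.766 × 0.880 = 0.67, but only if the outcomes were independent, which nothing in the article supports. That figure is an illustration.

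**Conclusion.** The concern holds. The article states two incompatible totals, 96 and 135, which differ by 39 patients (39/135 = 29%). The larger follows exactly from the stated inputs; the smaller has no derivation. At 96 randomised, each group starts below the plan's own minimum of 38 for UPDRS-III. Power for that outcome is 83% to 85% with no loss and 77% to 78% after 15% loss, so the type II error is roughly 22% to 23% where 10% was planned. MoCA is essentially unaffected.

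These powers rest on the article's differences and SDs taken at face value, a pairwise two-sided 5% comparison, and no gain from baseline adjustment beyond what the SDs may already contain. The contradiction itself rests on no assumption.

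**What to change.** State one target throughout. The abstract should read 135 patients, 45 per group, to agree with the Sample size calculation section. Any registry entry or flow-chart figure that carries 96 should be aligned as well; neither could be checked here, so this applies only if they differ.

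If 96 is the real target, revise the sample-size section instead. Withdraw the 90% claim for UPDRS-III and report the power at 96 after 15% loss: about 77% to 78% for UPDRS-III and 88% to 89% for MoCA on the stated SDs. If the sponsor wishes to rely on baseline adjustment, the assumed correlation must be given, together with a statement of whether the SDs are raw or adjusted.

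The first option is a text correction and adds nothing to the size already required. The second keeps the trial smaller but makes the stated power less favourable. Either should be settled before outcome data are seen, so that the choice between two published totals cannot look data-driven.

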**Discussion:**

The results of the study protocol will provide high-quality evidence for the potential of intervention measures based on the Yijinjing exercise to improve the cognitive and activity levels of Parkinson’s disease patients. We envision the Yijinjing exercise as a non-pharmacological family activity that can provide a new and more effective method for the treatment of Parkinson’s disease patients or those at risk.

**Clinical trial registration:**

This study was approved by the Ethics Committee of the Second Rehabilitation Hospital of Shanghai (2020-05-01). The trial has been registered in the China Clinical Trials Registry (ChiCTR2200055636).

## Introduction

Parkinson’s disease (PD) is a chronic progressive neurodegenerative disorder commonly seen in middle-aged and older adults individuals. The disease is characterized by motor symptoms such as bradykinesia, resting tremor, muscular rigidity, postural gait disorders, and non-motor symptoms such as cognitive and emotional disorders, sleep disorders, abnormal defecation, pain, and fatigue (1). PD is considered the second most common neurodegenerative disease globally according to the global burden of disease study (2, 3). In China, the prevalence of PD in people over 65 exceeded 1,700/100,000 from 1990 to 2016 (4), more than doubling the prevalence and exceeding that of any other country (5). Age is the primary risk factor for PD (6), and with the intensification of the aging wave, the disease’s prevalence continues to increase, leading to a significant economic burden on families and negatively impacting the quality of life of the older adults. Therefore, improving the clinical symptoms of PD patients has become a critical public health problem that needs to be addressed.

Currently, there is no practical way to cure PD completely, and drug therapy remains the primary treatment in clinical settings. However, various PD drugs may cause adverse reactions that could affect their therapeutic efficacy (7), which limits patients’ function and decreases their quality of life. While drug therapy cannot prevent or alleviate the process of PD neurodegeneration, it can manage related symptoms of the disease (8). Nonetheless, drug therapy alone is insufficient to meet clinical needs. In recent years, non-drug therapy for PD has gained increasing attention. Previous studies have shown that non-drug therapy can effectively improve the motor symptoms of PD patients and is a crucial strategy for treating non-motor symptoms, such as cognitive impairments that result in disability and reduced quality of life in most PD patients (9, 10). Combining drug and non-drug therapies through a multidisciplinary approach yields benefits beyond drug therapy alone (11).

Active participation in exercise training is a crucial non-drug intervention that can help improve the clinical symptoms of PD patients. Several studies have shown that exercise training can alleviate both motor symptoms (strength, endurance, balance, gait) and non-motor symptoms (cognition, depression, sleep) in PD patients (12–15). Exercise training can also improve cognitive performance and significantly reduce the risk of cognitive impairment or PD in middle-aged individuals, according to relevant laboratory studies (16, 17). However, the optimal type, intensity, duration, and mechanism of exercise training for PD patients still need to be determined. Nonetheless, previous studies have suggested that traditional Chinese exercises (TCEs), as medium-intensity aerobic exercise, can potentially prevent and improve older adults related diseases (18–20).

Yijinjing, an essential part of TCEs, combines movements, breathing and mindfulness, focusing on regulating the balance between body and mind to achieve a healthy state of the body. Moreover, Yijinjing has its unique advantages in TCEs, the 12 movements of the Yijinjing are mostly straight lines, and training requires practitioners to move slowly and coherently. Moreover, during movements training, each movement is relatively independent, and a complete set of movements can be trained, or the movements can be selectively trained according to the practitioner’s own needs. Currently, Yijinjing has demonstrated significant improvements in limb motor function, sleep disorders, cognitive function, and quality of life in older adults and convalescent stroke patients in the community (21–23). Moreover, previous studies have indicated that the Yijinjing has shown benefits in improving the cardiovascular system of the older adults and the motor function of patients with skeletal myopenia (24, 25). Therefore, Yijinjing has played a significant promoting role in improving cognitive and motor functions in the older adults population or patients with neurological diseases. This provides a new treatment method for improving cognitive and motor function in PD patients. However, there is little clinical report on the effectiveness of Yijinjing intervention in PD patients and its potential for treating PD remains to be developed.

Functional near-infrared spectroscopy (fNIRS) is a well-established non-invasive tool to continuously assess regional tissue oxygenation at bed-side. By measuring changes in the light absorption of different hemoglobin species, temporal changes in cerebral blood flow can be calculated with fNIRS. Several lines of evidence have shown that fNIRS is a validated tool for neurocognitive functions (26). Previous studies have suggested that the beneficial role of exercise, may be to facilitate neuroplasticity and improve motor learning. This may occur through enhanced blood flow and alterations in the brain environment (9). Moreover, since prefrontal cognitive circuits are critically involved in early phases of motor learning, another important component of exercise in PD is prefrontal cognitive engagement (9, 27). Therefore, We will observe the changes in cerebral blood oxygen signals between the prefrontal cerebral and sensorimotor cortex in PD during resting and task states using fNIRS.

The main objective of this study is to investigate the impact of a 12-week intervention using Yijinjing exercise on cognitive function, motor function, sleep quality, and quality of life in PD patients. Additionally, this study aims to monitor changes in prefrontal cerebral and sensorimotor cortex blood oxygen using fNIRS and explore possible mechanisms underlying the improvement of cognitive and motor functions in PD patients by this interventions. Based on our hypothesis, Yijinjing exercise could improve the cognitive and motor functions of Parkinson’s patients after 12 weeks of intervention and during a 1-month follow-up, as well as offering benefits for brain network connectivity function.

## Methods

### Study design

This single-center randomized controlled trial will be conducted at the Second Rehabilitation Hospital of Shanghai. Prospective participants will be screened for eligibility and voluntarily signing the informed consent form after invited to participate in the trial. Participants will be randomly assigned to the Yijinjing exercise group, brisk walking group, or control group in a 1:1:1 ratio. All patients will receive routine drug treatment and monthly health education for 12 weeks, while the intervention groups will receive Yijinjing exercise or brisk walking training. The primary outcome measures will be cognitive function and motor function assessed using the Montreal Cognitive Assessment (MoCA) and the Unified Parkinson’s Disease Rating Scale motor section (UPDRS-III), respectively. Secondary outcomes will include balance function assessed using the Berg Balance Scale (BBS), executive function assessed using the Trail Making Test (TMT), walking ability assessed using the 6-min walk test (6MWT), sleep quality assessed using the Pittsburgh Sleep Quality Index (PSQI), and quality of life assessed using the Parkinson’s Disease Questionnaire 39 (PDQ-39). Exploratory outcomes will include changes in cerebral blood oxygen signals in the prefrontal cerebral and sensorimotor cortex. Outcome measures will be collected before and after the interventions and after 1 month of follow-up. The assessor and data analyst will be blinded throughout the trial. The procedure is illustrated in Figure 1 and Table 1.

**Figure 1 fig1:**
[figure not shown]
Flow chart of the trial. PD, Parkinson Disease; fNIRS, functional near-infrared spectroscopy; Clinical scales includes: MoCA, Montreal Cognitive Assessment; UPDRS-III, Unified Parkinson’s Disease Rating Scale motor section; BBS, the Berg Balance Scale; TMT, Trail Making Test; 6MWT, 6-MinuteWalk Test; PSQI, Pittsburgh sleep quality index; PDQ-39, Parkinson’s disease questionnaire 39.

**Table 1 tab1:** Schedule of enrolment, intervention, and assessments.

Study period					
Time point	Enrolment	Baseline	Postallocation		Follow-up
	−1 week	0 week	1 week	12 week	1 month
**Enrolment**					
Eligibility screen	**×**				
Informed consent	**×**				
Descriptive information^*^		**×**			
Randomization		**×**			
Allocation		**×**			
**Intervention**					
Control group			**×**	**×**	
brisk walking group			**×**	**×**	
Yijinjing group			**×**	**×**	
**Assessments**					
MoCA^*^		**×**		**×**	**×**
UPDRS-III^*^		**×**		**×**	**×**
BBS^*^		**×**		**×**	**×**
TMT^*^		**×**		**×**	**×**
6MWT^*^		**×**		**×**	**×**
PSQT^*^		**×**		**×**	**×**
PDQ-39^*^		**×**		**×**	**×**
fNIRS^*^		**×**		**×**	**×**
Adverse events		**×**	**×**	**×**	**×**

^*^Descriptive information includes the personal general data, vital signs, history of present illness, clinical symptoms and signs, medical history, medication history and neurological examination. “**×**” means the item will be completed. MoCA, Montreal Cognitive Assessment; UPDRS-III, Unified Parkinson’s Disease Rating Scale motor section; BBS, the Berg Balance Scale; TMT, Trail Making Test; 6MWT, 6-MinuteWalk Test; PSQI, Pittsburgh sleep quality index; PDQ-39, Parkinson’s disease questionnaire 39; fNIRS, functional near-infrared spectroscopy.

### Sample size calculation

The design of this study is novel. According to the trial design and previous literature assessment, the sample size will be calculated based on hypothetical changes in MoCA score (28) or UPDRS motor score (10) at week 12. With a power of 90% and an alpha of 5% (two-sided). The SD from our feasibility study is used and our power calculation considered our planned analysis method, by means of an analysis of covariance (ANCOVA) in which baseline measurements served as a covariates, reducing the needed sample size (29). we calculated the minimum sample size (effect size = 0.3) in MoCA score (SD = 2.07, Difference = 1.8) to be 28 participants per group and UPDRS motor score (SD = 2.55, Difference = 1.9) to be 38 through PASS software (version 15.0.5). Therefore, With a 15% dropout rate considered, a total sample size of 135 participants will be necessary.

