### Statistical analysis

All primary and secondary analyses will be conducted on an intention-to-treat (ITT) basis. Modified ITT analysis included all randomized participants who completed at least 8 weeks of the intervention. Primary analyses will be conducted using multiple imputation methods for missing observations at baseline, post intervention, and at follow-up, assuming missing data are missing at random. Prespecified sensitivity analyses will be conducted for all participants using complete-case data at each time point.

Continuous data will be presented as mean ± SD or median ± quartile interval, while enumeration data will be presented as numbers and percentages. Between-group differences in demographic and baseline variables, as well as assessment variables, will be assessed using a chi-square test or the Fisher exact test for categorical variables and a one-way analysis of variance (ANOVA) or the Kruskal-Wallis test for continuous variables as appropriate. Intervention effects on primary and secondary continuous outcome measures will be compared by means of mixed repeated-measures analysis of variance, with and without adjustment for baseline and time-varying covariates (e.g., age, sex, and Hoehn and Yahr stage). Pairwise comparisons between the Yijinjing group and the two other groups will be conducted only if the omnibus F-test statistics indicated that the null hypothesis should be rejected. The primary analysis will to determine whether Yijinjing training improved the MoCA and UPDRS-III score compared with brisk walking training and control at 12 weeks. These continuous outcomes will be assessed by the 1-way analysis of variance model at 12 and 16 weeks. All statistical analyses will be conducted using SPSS software, version 24 (IBM). *p* value < 0.05 will be considered statistically significant. An independent statistician will carry out all statistical analyses.

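### The sample-size paragraph contradicts its own inputs and does not support 90% power for the gated, unadjusted 12-week analysis; the shortfall is in UPDRS-III

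*Protocol article*

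**What the plan says.** The Sample size calculation section sets its terms as "With a power of 90% and an alpha of 5% (two-sided"). It says of the variability that "The SD from our feasibility study is used", and that the calculation reflects the planned method, "by means of an analysis of covariance (ANCOVA) in which baseline measurements served as a covariates, reducing the needed sample size (29"). It then gives a "minimum sample size (effect size = 0.3) in MoCA score (SD = 2.07, Difference = 1.8) to be 28 participants per group" and a "UPDRS motor score (SD = 2.55, Difference = 1.9) to be 38". A 15% dropout allowance brings the total to 135. The section gives no baseline correlation or R-squared. It does not say whether the SDs are raw, change-score or residual, which arms the difference compares, or where the third mean lies.

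The Statistical analysis section makes the primary question Yijinjing against both brisk walking and control at 12 weeks. It assigns the 12- and 16-week outcomes to a one-way ANOVA, with no baseline covariate in that sentence. The comparisons of Yijinjing with the other two arms "will be conducted only if the omnibus F-test statistics indicated that the null hypothesis should be rejected". The same section also names a mixed repeated-measures ANOVA, with and without adjustment.

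**The concern.** Three things do not agree: the effect size of 0.3 and the difference and SD printed beside it; the ANCOVA reduction and group sizes that show no reduction; and a power figure with no three-arm structure behind it and a decision rule that has one. If the 90% belongs to a simple two-group comparison, it is not the power of the rule that will decide the trial.

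The walking comparison adds to this. The Introduction holds that "exercise training can alleviate both motor symptoms (strength, endurance, balance, gait) and non-motor symptoms (cognition, depression, sleep) in PD patients". A walking arm with no effect would sit badly with that rationale, yet only one difference is given per outcome, with no comparator named.

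**Working it through.** **Inputs.** From Sample size calculation: two-sided alpha 0.05, power 0.90; MoCA difference 1.8, SD 2.07; UPDRS-III difference 1.9, SD 2.55; dropout 15%. From Study design: three arms, 1:1:1. From Statistical analysis: one-way ANOVA, with pairwise tests only after a significant F.

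**1. Reproducing the stated sizes.** Unadjusted two-group normal approximation, n = 2(1.960 + 1.2816)² / d²:
- MoCA: d = 1.8/2.07 = 0.870; n = 27.8, rounded up to 28.
- UPDRS-III: d = 1.9/2.55 = 0.745; n = 37.9, rounded up to 38.
- Total: 38/0.85 = 44.7, so 45 per group, and 3 × 45 = 135.

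All three stated figures are reproduced with no covariate term.

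**2. What an ANCOVA reduction would look like.** If the SDs are raw, n is multiplied by (1 − r²). At an assumed r = 0.5: 27.8 × 0.75 = 20.8 (21) and 37.9 × 0.75 = 28.4 (29).

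**3. The effect size of 0.3.** For three equal arms, f = d/√6 when the means are evenly spaced and f = d√2/3 when one arm differs from two equal ones.

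| Outcome | d | f, evenly spaced | f, one arm differs |
|---|---|---|---|
| MoCA | 0.870 | 0.355 | 0.410 |
| UPDRS-III | 0.745 | 0.304 | 0.351 |

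So 0.3 fits MoCA, to which it is attached, on neither scale. It matches only UPDRS-III with evenly spaced means.

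**4. Power of the planned rule at 38 per group.** Simulation with at least 200,000 runs per case, the full stated Yijinjing–control difference, pooled three-arm error, no covariate gain, and unadjusted pairwise t-tests after a significant F:

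| Walking arm | UPDRS-III: omnibus F | UPDRS-III: gated, vs control | MoCA: gated, vs control |
|---|---|---|---|
| equals control | 92% | 87% | 96% |
| midway | 83% | 82% | 92% |

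If Yijinjing beats both arms by the full difference, the UPDRS-III power to win both gated comparisons is 82%. Reaching 90% for the gated UPDRS-III test against control without covariate gain would take 42 to 47 per group, depending on where the walking arm lies.

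**5. With a real baseline gain.** With R-squared = 0.20 on raw SDs (assumed), gated UPDRS-III power against control at 38 per group is 94% if walking equals control and 90% if it is midway.

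**6. Against walking.** If walking gives half the benefit (assumed), gated power for Yijinjing versus walking at 38 per group, unadjusted, is about 35% to 36% for UPDRS-III and 46% for MoCA.

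**The case against.** The strongest defence is that the group sizes may be ANCOVA figures after all. If the feasibility SDs are residual SDs, the formula in step 1 is already baseline-adjusted. A three-arm ANCOVA F-test with evenly spaced means and R-squared = 0.20 also returns exactly 28 and 38, and under that pattern UPDRS-III has f = 0.304, so 0.3 may simply stand beside the wrong outcome. This stands as far as it goes: a reader might infer that no ANCOVA reduction was taken, and the article does not prove that. But each rescue needs an input that the section does not state, and neither makes 0.3 right for MoCA.

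A reader might also infer that the trial lacks 90% power in general. It does not follow. MoCA at 38 per group is adequate against control even unadjusted, the UPDRS-III omnibus F alone reaches 92% when one arm differs, and baseline adjustment can close the gap. The Statistical analysis section also mentions an adjusted mixed model, but the sentence on the 12-week comparison names the unadjusted one-way ANOVA.

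The low power against walking depends on an assumed half-benefit. The Introduction speaks of exercise in general and gives no walking effect on either scale. Nor does the article plan any claim of equivalence from a null result.

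Finally, the omnibus gate is not itself an error. With three arms it controls the familywise error within an outcome, so replacing it is a matter of preference.

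**Conclusion.** The point holds in this limited form. The effect size of 0.3 is wrong for the MoCA inputs it accompanies, and the credited ANCOVA gain is neither visible nor documented. The stated 90% is not supported for the gated test under the unadjusted one-way ANOVA: UPDRS-III, which sets the trial's size, has about 82% to 87% against control at 38 per group. The shortfall is modest, is confined to UPDRS-III for the comparison with control, and disappears if baseline explains about 20% or more of the variance and the analysis uses it. Power against walking is undocumented and could be much lower, but how much lower depends on an effect that the article does not give.

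These figures take the SDs as raw with no covariate gain, and assume the 135 patients of the Sample size calculation section. The Abstract plans 96, which is a separate discrepancy.

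**What to change.** - Delete the effect size of 0.3, or give the correct value for each outcome with its scale (d or f) and the assumed pattern of means.
- State whether the SDs are raw, change-score or residual, and the baseline correlation credited.
- Make the 12-week primary analysis the baseline-adjusted ANCOVA that the Sample size calculation section says was planned, in place of the unadjusted one-way ANOVA.
- Restate power for the gated test separately for Yijinjing versus control and Yijinjing versus walking, with the walking effect shown as a range and labelled as an assumption.
- Optional: a fixed sequence (control first, then walking) instead of the omnibus gate. It removes the gate's cost for the first comparison but does not cure low power against walking.

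The cost is a recalculation, some rewording, and a less favourable stated power for the walking comparison. If the baseline gain is real and used, the 135-patient calculation need not grow on account of the control comparison.
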